### Pilot study

A small-scale pilot study will be carried out in one low-income community in Shanghai. We will recruit 20 BC survivors according to our inclusion criteria and baseline assessment will be done before intervention. After that, the MBSR intervention program will be offered to each subject as a group session. At the end of 8-week intervention, all subjects will be reassessed. We will also collect subjects’ feedback regarding the intervention program. On the basis of the experience and feedback:We will modify the content of MBSR, if needed, in order to make it more suitable for Chinese BC survivors.We will revise our assessment instruments according to subjects’ feedback.

### Procedures to ensure compliance with ethical standards

All participants will be asked to provide written informed consent and will be assured of anonymity and confidentiality. In this letter, apart from the brief introduction of this project, subjects will be informed about the detailed rules on the protection of their information, as follows: (1) each investigator in this project will be requested to sign a confidentiality agreement to ensure that they will not disclose information of subjects; (2) research data will be collected with absolute anonymity and confidentiality; and (3) only registered investigators can access the data and outcomes.We have research ethics approval from Ethics Committee of Fudan University School of Public Health, and the IRB Approval Number is 2014-TYSQ-09-1.

## Discussion

The largest threat to our study’s internal validity is the possible “contamination effect” (or spillover effect) between the two trial arms. As our participants will be recruited from 10 low-income communities from two of Shanghai’s poorer districts, it is possible that some of these participants know each other and may hold discussions regarding the MBSR treatment. The contamination effect could compromise measurable differences between the two trial arms and bias the intervention result toward the null hypothesis. However, as MBSR takes a substantial amount of exercise to achieve measurable results in mental health, it is unlikely that contamination alone could diminish the difference between those who attend the class and those who only hear about the practice. Plus, we will communicate to the waitlist control group in written materials to make sure that they start MBSR practice only when they receive the intervention.

**Table 1 Tab1:** Summary of methods used for each hypothesis

Objective (main study)	Hypothesis	Method
Objective 1	Primary Hypothesis 1: Improvement in mental health, quality of life, and medication treatment compliance in mindfulness-based stress reduction (MBSR) group	Method 1: Bivariate analyses and ANCOVA
	Primary Hypothesis 2: Relation between MBSR and improvement	Method 2: Mediation analysis in structural equation modeling
Objective 2	Secondary Hypothesis: Long-term improvement of MBSR	Method 3: Repeated measures analysis
Objectives 3 and 4	N.A.	Expert consultation

There is also the possible threat to internal validity through high attrition among participants. Attending an 8-week course is not a trivial matter for young working women, and thus it is possible that those who do not experience an immediate gain in mental health are more likely to quit. This possible pattern of selective attrition could lead to overestimation of intervention impact, as most of those who stay until the end of the intervention are more likely to experience MBSR benefits. We believe, however, that our financial incentive for participants should be sufficient for most BC survivors to complete the course, so long as we appropriately program the timing of our financial incentive (e.g., payment will be given out at each session, instead of being given out in a lump sum at the beginning).

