#### Usual care regimen

Subjects randomized to the waitlisted control group will receive no formal intervention, but will continue to have standard post-treatment clinic visits according to their treatment plans. Additionally, to avoid possible overlap (contamination) with components of the MBSR program, the investigators will specifically ask subjects in the waitlisted control group not to start mindfulness-based practice during the study period.

MBSR intervention will be offered to each usual care subject after 6 months follow-up. They will be provided with a brief orientation to MBSR (BC), a manual on the program, and a 2-month practice class after post-assessment.

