### Statistical methods

We will compare the outcome variables (SDS, SAS, MAAS, Quality of Life Index, and MMAS) between the two groups using the χ^2^ test for categorical variables and Student t or Wilcoxon tests for continuous variables. Analysis of covariance (ANCOVA) will be conducted to assess whether MBSR is related to changes between baseline and after 8 weeks of intervention in relation to psychological status, QOL, and compliance behaviors.We will use a structural equation model [45] to examine the intervening role of mindfulness enhancement on improving mental health, QOL, and compliance with medical treatment. Mediation analysis, as implemented in MPlus 7.11, will be used to analyze the causal pathway from MBSR intervention to health outcomes through mindfulness enhancement.We will use a random-effects repeated measures analysis [46] to examine the impact of MBSR intervention on health outcomes, compliance behavior, adjusting for confounding variables (age, education, household income, occupation, previous cancer history, and household registration status: Shanghai vs. non-Shanghai). The repeated measure analysis approach accounts for the same individual’s different outcome measures across different points in time without assuming either linear or curvilinear growth pattern. Cronbach alpha’s will be computed to determine the internal consistency of our outcome measures. Using this approach (as implemented by the PROC MIXED and PROC GLIMMIX modules in SAS 9.0), we have published an article analyzing a famous randomized controlled trial of lung cancer screening, which shows a behavioral differential between the two trial arms [47].

The relationship between methods used for each hypothesis is shown in Table 1.

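### The named remedy for selective dropout acts on class attendance, and the 8-week analysis for primary hypothesis 1 does not use the 4-week score that could reduce the predicted bias

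*Protocol article*

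**What the plan says.** The Discussion of the protocol article names high attrition as a threat to internal validity. It considers it possible that "those who do not experience an immediate gain in mental health are more likely to quit", and draws the consequence: "This possible pattern of selective attrition could lead to overestimation of intervention impact". Its reply is the belief that "our financial incentive for participants should be sufficient for most BC survivors to complete the course", provided the timing is right. The example of good timing is that "payment will be given out at each session, instead of being given out in a lump sum at the beginning".

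Under Usual care regimen, "Subjects randomized to the waitlisted control group will receive no formal intervention", and "MBSR intervention will be offered to each usual care subject after 6 months follow-up". Under Implementation, all subjects are reassessed at 4 weeks, 8 weeks, 6 months and 12 months. Follow-up is by telephone, with no condition that the woman still attends class.

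Statistical methods states: "Analysis of covariance (ANCOVA) will be conducted to assess whether MBSR is related to changes between baseline and after 8 weeks of intervention". Table 1 assigns bivariate analyses and this ANCOVA to primary hypothesis 1. The same section plans a random-effects repeated measures analysis of the intervention's impact, which Table 1 lists against the secondary hypothesis. That hypothesis compares the MBSR group at 1 year with its own baseline.

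**The concern.** The protocol predicts a bias in favour of the intervention, but the remedy it names works at a different point from where the bias arises. Overestimation comes from missing 8-week outcomes among women who did not improve. Payment at sessions encourages attendance and reaches outcome completeness only indirectly. Because the waitlist arm has no sessions before 6 months, an incentive of that form could also make retention differ between arms at the time points that matter for the randomised comparison.

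The analysis assigned to primary hypothesis 1 adds to this. The protocol's own account is that absence of an early gain drives quitting, and the 4-week assessment is where that would be seen. As described, the 8-week ANCOVA uses the baseline and 8-week scores only. A model that can use the 4-week score is already in the plan but is assigned elsewhere. At stake is a false or inflated claim of benefit on the main hypothesis.

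**Working it through.** **1. The plan's own attrition figure.** Sample size gives 195 per group, 390 in total, and 10% attrition. 390 × 1.10 = 429, which reproduces the stated recruitment target. (Dividing instead gives 390 / 0.90 = 433.3, so 434.) This allowance protects power. It does nothing about the direction of losses. The figure of 195 cannot itself be reproduced, because SD, alpha, power and correlation are not stated.

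**2. Yardstick: effect detectable with 195 per group.** Assumed: two-sided 0.05, one time point.

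d = (z for 0.975 + z for power) × √(2/195), with √(2/195) = 0.1013.

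- 80% power: (1.960 + 0.842) × 0.1013 = 0.28 SD
- 90% power: (1.960 + 1.282) × 0.1013 = 0.33 SD

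Applied to the cited difference of 50.3 − 46.9 = 3.4 points, these imply an SD of about 12.0 or 10.4.

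**3. Bias if women with poor early change lose their 8-week score.** Assumed: true effect zero; a fraction q of the MBSR arm with the worst early change has no 8-week score; control losses are at random; r is the correlation between early change and the 8-week residual. The mean of the observed MBSR scores shifts by

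b = r × φ(z_q) / (1 − q).

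For q = 0.10, φ(−1.282) / 0.90 = 0.195. For q = 0.20, the factor is 0.350.

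The false-positive rate is Φ(b/se − 1.96) + Φ(−b/se − 1.96), with about 214 allocated per arm (429 / 2) and 10% random loss in controls. At q = 0.10, se = √(2/192.6) = 0.102.

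| q | r = 0.3 | r = 0.5 | r = 0.7 |
|---|---|---|---|
| 10%: bias (SD) | 0.058 | 0.097 | 0.136 |
| 10%: false-positive rate | 8.9% | 16.0% | 26.8% |
| 20%: bias (SD) | 0.105 | 0.175 | 0.245 |
| 20%: false-positive rate | 17.0% | 38.4% | 64.5% |

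At 10% the bias runs from 0.058 / 0.328 = 18% to 0.136 / 0.284 = 48% of the detectable effect. The 20% rows go beyond the protocol's assumed attrition and show sensitivity only.

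**4. Does the 4-week score help?** A simulation of 400,000 women had no true effect and equal correlation among baseline, 4-week and 8-week scores. The 20% of the MBSR arm with the worst change to 4 weeks lost their 8-week score.

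| Correlation | ANCOVA on observed 8-week scores | Estimate also using 4-week scores |
|---|---|---|
| 0.5 | 0.094 SD | −0.0005 SD |
| 0.7 | 0.098 SD | −0.0016 SD |

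The second column predicts missing 8-week scores from baseline and 4 weeks within arm, which is in effect what a likelihood-based mixed model does when missingness depends on observed scores. The bias disappears because, in this set-up, loss depends only on scores that were observed.

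**The case against.** The strongest reply is that quitting the course is not the same as a missing outcome. Implementation has every woman telephoned at every time point. If those who leave class still answer, this bias does not arise. That stands: the bias needs a second step, that some women who quit also miss the 8-week call. The protocol's own concern about overestimation presupposes that some do.

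Three stronger readings are tempting, and the documents do not support them.

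- **That payment is the only safeguard.** It is the only one named against attrition, but telephone follow-up of all subjects and the repeated-measures model are both in the plan.
- **That a paid arm is compared with an unpaid arm, so that cash is confounded with treatment.** Payment at each session is given as an example of timing, the incentive is described for participants in general, and payment of waitlisted women for assessments is neither stated nor excluded. No amount is given. An effect of cash on the socioeconomic domain of the Quality of Life Index is therefore speculation.
- **That the ANCOVA is a completers' analysis.** The protocol does not say how women without an 8-week score are handled. Such a rule may sit in an analysis plan or full protocol not shown, and its absence is no finding.

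It is also fair that the size rests on assumed dropout patterns, and that paying for attendance serves a legitimate aim, completion of the course.

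**Conclusion.** The point holds in a limited form. The protocol predicts upward bias, names a remedy aimed at attendance rather than outcome completeness, and assigns to primary hypothesis 1 an 8-week analysis that, as described, leaves out the 4-week score. The model better suited to the predicted pattern is already planned, but Table 1 assigns it to the secondary hypothesis.

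The illustrative size is 0.06 to 0.14 SD at 10% selective loss, against 0.28 to 0.33 SD detectable. It rests on selective loss in the MBSR arm only, the assumed correlations, and quitters also missing the 8-week assessment. None of these can be checked from the document. If women who leave class are all assessed, the bias is nil.

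**What to change.** For primary hypothesis 1, estimate the 8-week difference between arms from the planned repeated-measures mixed model. Use the baseline, 4-week and 8-week scores and include all allocated women by assigned arm. Amend Table 1 to match. Because women may also leave for reasons that the observed scores do not carry, add a sensitivity analysis that sets missing MBSR outcomes to waitlist-like values (reference-based imputation).

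Separately, offer any incentive for completing outcome assessments equally in both arms.

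The trial had not begun at the time of writing. The cost is a little more analysis work and, if the budget is fixed, a somewhat smaller incentive to attend class. That second cost is a genuine trade-off; the change of model is nearly free.

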## Trial status

At the time of writing of this manuscript the trial had not yet begun. We are currently applying for financial support.

## Abbreviations

MBSR: Mindfulness-based stress reduction, an intervention to reduce the stress by mindfulness
BC: Breast cancer
QOL: Quality of life
